# Transcranial direct current stimulation as treatment for major depression in a home treatment setting (*HomeDC* trial): study protocol and methodology of a double-blind, placebo-controlled pilot study

**DOI:** 10.1186/s40814-023-01423-x

**Published:** 2023-12-15

**Keywords:** Non-invasive brain stimulation, tDCS, Major depressive disorder, Home-based treatment, Home treatment, Remote control

## Abstract

**Introduction:**

Transcranial direct current stimulation (tDCS) of prefrontal cortex regions has been reported to exert therapeutic effects in patients with major depressive disorder (MDD). Due to its beneficial safety profile, its easy mode of application, and its cost-effectiveness, tDCS has recently been proposed for treatment at home. This would offer new chances for regionally widespread and long-term application. However, tDCS at home must meet the new methodological challenges of handling and adherence. At the same time, data from randomized controlled trials (RCT) investigating this mode of application are still lacking. In this pilot RCT, we therefore investigate the feasibility, safety, and effectiveness of a new antidepressant tDCS application set-up.

**Methods and analysis:**

The *HomeDC* trial will be conducted as a double-blind, placebo-controlled, parallel-group design trial. Thirty-two study participants with MDD will be randomly assigned to active or sham tDCS groups. Participants will self-administer prefrontal tDCS for 6 weeks. Active tDCS will be conducted with anode over F3, cathode over F4, for 5 sessions/week, with a duration of 30 min/day, and 2 mA stimulation intensity. Sham tDCS, conversely, follows an identical protocol in regard to electrode montage and timing, but with no electric stimulation between the ramp-in and ramp-out periods. Both conditions will be administered either as a monotherapy or an adjunctive treatment to a stable dose of antidepressant medication. Adjunctive magnetic resonance imaging (MRI) and electric field (E-field) modelling will be conducted at baseline. Primary outcome is feasibility based on successfully completed stimulations and drop-out rates. The intervention is considered feasible when 20 out of 30 sessions have been fully conducted by at least 75% of the participants. Effectiveness and safety will be assessed as secondary outcomes.

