## Methods

### Design

The study will be conducted in a double-blind, placebo-controlled, parallel-group design with 20 study participants per group. This trial will take place at the Department of Psychiatry and Psychotherapy of the Ludwig-Maximilians-Universität Munich (LMU). Participants with a primary MDD diagnosis according to the Diagnostic and Statistical Manual of Mental Disorders, 5th Edition (DSM-5), will perform a 6-week self-administered treatment with prefrontal active tDCS or sham tDCS at home; either as a monotherapy or as an adjunctive treatment to stable antidepressant medication. Participants will be divided (1:1) into two groups by fixed-blocked randomization, each group receiving either active tDCS or sham tDCS for a total of 6 weeks (5x/week, maximum 30 sessions). At baseline, optional cranial MRI (cMRI), consisting of structural MRI (sMRI) and functional MRI (fMRI), will be performed. E-field modeling, based on the cMRI scans, may also take place. During the treatment phase, a study visit will take place every 2 weeks. An additional study visit will take place after the first week addressing any difficulties with self-application at home. After 6 weeks, the primary endpoint will be reached concluding the treatment phase. The final rating will be made in the ensuing follow-up phase, consisting of study visit 5 and 6 (V5) (V6). V5 and V6 will take place 4 weeks and 8 weeks, respectively, after the last stimulation session (Fig. 1). According to the *DepressionDC* trial [41], a total of 4 sessions may be missed without denoting a drop-out. Missed sessions can be compensated with additional sessions in week 7. All devices used in this study have CE certifications.

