### Power analysis and sample size calculation

Considerations of adequate sample size for feasibility outcomes draw on previous study results, with sample sizes varying from case series [27, 45] to larger randomized controlled trials with up to 64 participants [28, 47]. The dropout rate or rate of missed stimulations also varies depending on the study protocol. A similar study protocol with only 4 weeks of stimulation plus taper phase (32 stimulations in total) was used by Alonzo and colleagues [26]. This study, albeit without sham control, involved 34 participants and resulted in a drop-out rate of 6% with 93% of sessions completed. Similar numbers were found in the trial of Woodham and colleagues. Of 26 participants included, 92.3% completed the 6-week treatment phase [30]. Thus, with respect to feasibility, a comparable sample was intended.

Regarding the antidepressant effects, a power calculation was performed based on the amputated intention-to-treat (ITT) sample of the SELECT trial [7]. The data set from this trial was available to our group for sample size calculation. The change in MADRS score between the placebo-medication/sham tDCS condition and the sertraline (50 mg)/active tDCS condition was used. A change in the MADRS score was hypothesized because the effects of tDCS are thought to be synergistic with existing serotonergic medication [48]. In this pilot study, participants should have been on stable medication for at least 2 weeks or be medication-free. Thus, at baseline, they had not yet responded adequately to existing medication as seen in a minimum HDRS-17 score of 13. Only active tDCS is expected to have a synergistic effect [49]. Since the 50 mg sertraline was a very low dose, the synergistic effect in the SELECT study [7] is questionable, but it can be assumed that study participants with stable serotonergic medication get such an effect, so that with the assumption of the effects of the two groups the achieved effect is not overestimated.

The difference of change in MADRS scores (pre-post treatment phase) between the two groups was *M* = 12.58 points. The standard deviation of the change was SD = 11.01 points. After week 6, this leads to a Cohen’s *d* of 1.14. With power = 0.90 and a two-sided test, the G*Power analysis results in a required participant number of 18 per group.

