Assuming a significance level of *α* = 0.05 and power = 0.90, a total sample size of 36 study participants would detect a true group difference of 12.58 MADRS points. Further taking a drop-out rate of approximately 10% into account leads to a total recruitment number of 40 study participants.

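### The abstract randomises 32 participants, but the Design and sample size sections plan 40, and 32 does not give the stated 90% power

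*Protocol article*

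**What the plan says.** Three places in the protocol article give the planned size.

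- **Abstract, Methods and analysis:** "Thirty-two study participants with MDD will be randomly assigned to active or sham tDCS groups".
- **Methods, Design:** the trial has a "parallel-group design with 20 study participants per group". Allocation is 1:1, so the total is 40.
- **Methods, Power analysis and sample size calculation:** the calculation uses a between-group difference in MADRS change of 12.58 points. It adds that "The standard deviation of the change was SD = 11.01 points", and gives Cohen's d as 1.14. It then states: "With power = 0.90 and a two-sided test, the G*Power analysis results in a required participant number of 18 per group". That makes 36 in total at alpha 0.05. The section ends: "Further taking a drop-out rate of approximately 10% into account leads to a total recruitment number of 40 study participants".

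The primary outcome in the abstract and in Study objectives is feasibility: at least 75% of participants fully completing 20 of 30 sessions. The MADRS comparison, to which the power calculation belongs, is secondary there.

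**The concern.** All three statements are current, forward-looking text about the same quantity, and they cannot all be right. The abstract's 32 is a number randomised, so it cannot be read as a count of evaluable participants or completers.

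Three things depend on which number holds:

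- **When recruitment is complete.** With two published targets, a trial that stops at 32 could be reported as fully recruited or as 8/40 = 20% short. A stop anywhere from 32 to 40 could be defended afterwards. The article does not plan an early stop; the problem is the ambiguity.
- **The power claim.** The 90% is derived for 36 evaluable participants. If only 32 are randomised, the claim is not supported on the plan's own assumptions.
- **The feasibility count.** The 75% rule means 0.75 × 40 = 30 participants, or 0.75 × 32 = 24.

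**Working it through.** **Inputs**, all from the sample size section: difference Δ = 12.58 MADRS points, SD = 11.01, two-sided α = 0.05, power 0.90, drop-out about 10%. The 1:1 allocation is from the Design section.

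**Step 1. Effect size.** d = 12.58 / 11.01 = 1.143, which the article rounds to 1.14.

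**Step 2. Reproduce the plan's figure.** For a two-sample t test, power comes from the noncentral t distribution with noncentrality δ = d × √(n₁n₂/(n₁+n₂)) and n₁+n₂−2 degrees of freedom. Solving for 90% power gives n = 17.1 per group (17.2 with d = 1.14), rounded up to 18. The total is 2 × 18 = 36, and 36 / 0.9 = 40. The article's 18, 36 and 40 all reproduce.

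**Step 3. Look for a derivation of 32.**

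- 40 less 10% is 36, not 32.
- 32 inflated for 10% loss is 32 / 0.9 = 35.6, so 36 would be recruited. Thirty-two as an evaluable number therefore does not lead to 40 either.
- The optional MRI subset is 20.
- Under the stated two-sided test, 16 per group does not reach 90% (Step 4). A one-sided test would reach it, but the article specifies a two-sided one.

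**Step 4. Power at each size** (two-sided t test, d = 1.143).

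| Scenario | n per group | δ | Power |
|---|---|---|---|
| 40 randomised, no loss | 20 / 20 | 3.61 | 94.1% |
| 40 randomised, 10% loss (36) | 18 / 18 | 3.43 | 91.5% |
| 32 randomised, no loss | 16 / 16 | 3.23 | 87.8% |
| 32 randomised, 10% loss (29) | 14 / 15 | 3.07 | 84.2% |
| 32 randomised, 10% loss (28) | 14 / 14 | 3.02 | 82.9% |

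The 28 to 29 evaluable come from 32 × 0.9 = 28.8. Using d = 1.14 instead of 1.143 changes each power by less than 0.2 percentage points.

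**Step 5. Difference detectable with 90% power.** This is 12.2 points with 18 per group, 13.0 with 16 and 14.0 with 14. Only 18 per group brings it below the assumed 12.58.

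**The case against.** The case on the other side does not deny the contradiction, but argues that its consequences are small.

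- **The body of the article is consistent.** The Design and sample size sections agree and reproduce, and the outlier is one abstract sentence without a derivation. The likeliest explanation is an uncorrected abstract. That is plausible but unproven, and the abstract would still need correcting.
- **Power concerns a secondary outcome.** For feasibility, the sample size section asks only for a sample comparable with earlier studies of 34 and 26 participants, and 32 lies between them. This is correct: the power argument does not touch the feasibility objective. It does touch the only formal calculation in the article. The Assessments section also labels the MADRS as primary outcome.
- **The shortfall is modest and may vanish.** With no loss it is about 2 points, and a normal approximation gives 89.8%. The planned ANCOVA adjusts for baseline. Taking a correlation r between baseline and change as an assumption, and reducing the SD by √(1−r²), 90% is regained at r of about 0.27 with 16 per group and about 0.41–0.44 with 28–29 evaluable. The article gives no such correlation and its calculation does not use one, so this gain cannot be credited. The 83–84% is therefore the power of an unadjusted t test, and should be labelled so.
- **The feasibility rule is a percentage.** The article nowhere states 30 of 40. The rule stays the same; only the implied count changes.
- **Selective stopping is conjecture.** No interim look is described, and participants, operators and raters are blinded. That makes a stop guided by the group difference unlikely, but leaves the end of recruitment undefined.

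**Conclusion.** The concern holds. The article states two planned sizes, 32 and 40, and offers nothing to reconcile them. Only 40 fits the stated 18 per group, the 36 evaluable, the 10% drop-out allowance and the 90% power.

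If 32 were the real target, power would be 87.8% with no loss and about 83–84% with the plan's own drop-out. This assumes d = 1.143, a two-sided alpha of 0.05 and an unadjusted two-sample t test. The loss against the 91.5% at 36 evaluable is about 4 points in the first case and 7 to 9 in the second.

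The document does not show which number was intended. The power shortfall is conditional on 32 being the target, whereas the contradiction is not conditional on anything. Because it concerns the planned number randomised, it must be corrected.

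**What to change.** State one planned number randomised, the same in the abstract, the Design section and the sample size section.

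- **If 40 stands:** change the abstract sentence to 40 (20 per group). Nothing else moves.
- **If 32 is the real target:** change the Design and sample size sections to 16 per group. Restate the power for the MADRS difference of 12.58 points as 87.8% with no loss and about 83–84% after 10% drop-out, labelled as an unadjusted two-sample t test. If a gain from baseline adjustment is claimed, give the assumed correlation and its source. Explain why the target was reduced.

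In either case, it helps to give the count implied by the 75% feasibility rule (30 of 40, or 24 of 32). The rule itself needs no change.

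The cost is a wording correction and, in the second case, a less favourable power statement. No extra participants or procedures are needed.

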**Discussion:**

In the *HomeDC* trial, the technical requirements for a placebo-controlled tDCS study in a home-based treatment setting have been established. The trial addresses the crucial points of the home-based tDCS treatment approach: uniform electrode positioning, frequent monitoring of stimulation parameters, adherence, and ensuring an appropriate home treatment environment. This study will further identify constraints and drawbacks of this novel mode of treatment.

**Trial registration:**

www.ClinicalTrials.gov. Trial registration number: NCT05172505. Registration date: 12/13/2021.

## Background

Major depressive disorder (MDD) is a disorder with a high prevalence. It is one of the leading causes of work disability worldwide [1]. For the treatment of MDD, psychotherapy and/or pharmacotherapy are recommended, depending on the severity of the disease. While pharmacotherapy is available almost everywhere, it is not suitable for all patients and is sometimes associated with considerable side effects or even intolerance [2]. Psychotherapy is not always readily available. Furthermore, approximately 33% of patients suffering from MDD have a treatment-resistant course even after guideline-appropriate stepwise therapy and do not respond adequately to pharmacological interventions [3].

Possible non-drug therapies for MDD include non-invasive transcranial brain stimulation (NIBS) techniques. NIBS techniques are well established in experimental neurosciences and have been increasingly used in recent years in the treatment of psychiatric diseases, especially depressive disorders [4, 5].

Studies on the antidepressant efficacy of transcranial direct current stimulation (tDCS) show promising, but not fully consistent, results. Two large, randomized, double-blind, placebo-controlled trials [6, 7] demonstrated significant antidepressant effects within several weeks of treatment with tDCS compared with sham stimulation. Meta-analyses on the topic also confirm the efficacy of tDCS over placebo in the treatment of MDD [8, 9].

The major advantage of tDCS over the other main NIBS technique, transcranial magnetic stimulation (TMS), is its applicability in a wide range of settings. From its use in magnetic resonance imaging (MRI) scanners to its therapeutic application as a treatment at home, the latter having been poorly investigated in studies thus far [10]. TDCS also has a very favourable side effect profile with a low incidence of complications [11]. The possibility of tDCS home-based treatment has already been discussed for some years now, and solutions for the technical requirements of its implementation have been developed and presented [12, 13]. At home tDCS treatment is convenient, given limited psychotherapy availability for MDD, as well as the current pandemic, COVID-19, also limiting frequent clinic contact.

So far, the few studies and case reports published on tDCS treatment at home have mainly investigated its neurological applications [14–16], for example, the treatment of cognitive impairment and fatigue in Parkinson’s disease, cerebellar ataxia, chronic pain, fibromyalgia, tinnitus, and in apallic patients [13–19]. In sum, results of the described case reports show good feasibility. Severe side effects were not reported, with larger case series showing a satisfactory degree of safety [20]. Reviews on the topic confirm these findings and highlight new monitoring opportunities [10, 21]. No serious therapeutic side effects were found in the 19 studies reviewed by Sandran et al. [21].

In the psychiatric field, two patients with paranoid schizophrenia had successful partial remission of previously treatment-resistant multimodal hallucinations using at home tDCS [22, 23]. These aforementioned studies represent the majority of research on at home tDCS, which is mostly centered around neurological disorders and certain psychiatric conditions. In the following, we will highlight the few published studies examining the treatment of depression with at home tDCS. One of these few studies is a placebo-controlled trial investigating the home-based application of prefrontal tDCS in 26 participants. These participants presented with temporal lobe epilepsy and depressive symptoms. There was a total of 20 sessions, 20 min each, at an intensity of 2 mA. Results showed good feasibility, but no significant difference between the groups in regard to the reduction of depressive symptoms [24]. In another home-application MDD case series, 12 trial participants with treatment-resistant, chronic depression were treated with tDCS. This served partly as maintenance therapy after electroconvulsive therapy (ECT) or repetitive TMS. After at least 6 weeks of treatment, significant improvements in depressive symptoms were observed. The effects lasted in part for several months [25]. In an open label, home-based tDCS trial by Alonzo and colleagues [26], with the same protocol as *HomeDC*, 34 trial participants with unipolar and bipolar depression conducted a minimum of 24 tDCS sessions. Overall, this pilot trial addressed the issues of electrode positioning, supervision, training, and control of adherence. There was improvement in depressive symptomatology (response rate of 38%), the drop-out rate was very low at 6%, and side effect outcomes were similar to tDCS studies in a clinic setting [26]. However, a control condition was lacking in this pilot study. Another case series combined home-based tDCS (bifrontal montage, 21 sessions over 6 weeks) with app-based psychological intervention in five participants with MDD [27]. Safety and feasibility were good with a response rate of 80%, even in combination with the app-based intervention. Technical parameters were not monitored. In the largest home-based tDCS trial for MDD to date, a placebo-controlled, single-blind design was used to stimulate the prefrontal cortex in 58 trial participants with MDD (2 mA, 30 min, 6 weeks) [28]. Results showed feasibility and a significant reduction in the Beck Depression Inventory (BDI) in the active tDCS group. Some methodological limitations, e.g., the single-blind design and simultaneous administration of varying escitalopram dosages have to be considered. In another small pilot study, ultimately, only three participants underwent the study protocol investigating the safety and feasibility of a home-based, “study companion-administered” tDCS intervention [29]. Another very recent study confirmed the feasibility and safety of home treatment with tDCS in an open label design without placebo control. Here, the same parameters as the *HomeDC* trial were used for 6 weeks in 26 participants. Antidepressant effects were promising and long lasting with 91.3% clinical response and 73.9% remission rates even at the 6-month follow up [30].

Looking forward, we await the findings of further studies. The study protocols of these larger randomized controlled trials (RCT) have already been published, partly combining tDCS with cognitive training and behavioral therapy. The results of these specific trials are expected in future and will be a welcome addition to the results of the pilot studies, case reports, and smaller monocentric single-blind trials highlighted above [31, 32].

The following guidelines for the home-based use of tDCS helped navigate issues encountered during the design of the *HomeDC* study [33]:Training and supervision. A checklist [26] and instructional videos are helpful for making training easier, standardizing procedures, and play an important role in tele-health solutions [34]. The common usage of assisted home treatment via a caregiver or family member appears effective in treating physically impairing or neurological diseases [27]. This approach however is not conducive to the treatment of MDD. As the goal is to save resources and increase patient autonomy at home.Electrode positioning. Different technical solutions were tested and have been selected to combine the highest possible degree of accuracy and individuality with ease of user [22, 23, 35–38].Monitoring adherence to the tDCS protocol. Here, we find various options ranging from personal consultations and pre-programmed block times to monitoring stimulation times and duration.Safety monitoring and assessment of targeted outcomes. Outcomes in the psychiatric field are most accurately measurable through personal ratings. Monitoring technical stimulation parameters could contribute to safety monitoring and stimulation quality. A more personnel-intensive option would be assisted stimulation.

Grounded in these critical points, particular strengths of the *HomeDC* trial design are cloud-based supervision of technical data and timing, new caps offering standardized electrode positioning, and individualized dosage through approximated modeling of electric field (E-field) intensity based on individual MRIs.

With cloud-based monitoring and supervision of the technical data, the study provides a contribution to technical achievements, which will allow us to draw objective conclusions about the quality of the stimulations performed. Variability in impedance, current, and voltage will be correlated with clinical outcome to find further possible factors influencing the effectiveness of tDCS. It will also be possible to compare the technical data of the *HomeDC* trial with that of the *DepressionDC* trial, a large scale RCT covering in-clinic tDCS in MDD [39]. Thus, contrasting stimulation quality between home-based, self-administered tDCS and on-site application by an operator (*DepressionDC*). The time tag of the stimulations will be used to check the adherence.

For correct and easy electrode montage in the *HomeDC* trial, caps with integrated electrodes have been developed. Unlike most contemporaries, these take into account not only the head circumference, but also the distance between the external eye angle and the Cz electrode point; as the exact positioning of the electrodes is crucial for correct tDCS stimulation of the target [40].

Using these standards in a placebo-controlled, double-blind, randomized design, the *HomeDC* trial aims to investigate the feasibility, safety, and effectiveness of prefrontal tDCS as an at home treatment for MDD. In addition, the *HomeDC* trial adopts and tests a cloud-based approach for supervising timing and technical data, recently innovated by the *DepressionDC* trial [39].

